#### Count Data

3.3.3

Count data (intensive care unit length of stay, hospital length of stay, duration of intubation, days without delirium treatment) will be analyzed using the Wilcoxon rank‐sum test. Results will be presented as medians with interquartile ranges and 95% confidence intervals for the median difference obtained by bootstrapping.

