### Sample Size

2.6

The trial aims to include 1000 patients across five sites, covering the entire Danish population. Sample size calculations were performed separately for each intervention based on its primary outcome.

For the Dexamethasone and backrest elevation interventions (primary outcome: 90‐day mortality), assuming an overall mortality of 35% and a 25% relative risk reduction (to 26% mortality), with 85% power and a two‐sided significance level of 5%, 468 patients per group are required. To account for potential dropouts and loss to follow‐up, 500 patients per group (1000 total) are planned.

For the olanzapine and early wakeup interventions (primary outcome: days alive outside hospital within 30 days), estimates assumed 35% mortality during initial hospitalization (0 days alive outside hospital) and a mean of 15 days outside hospital for survivors, yielding a population mean of 9.8 days with an estimated standard deviation of 7 days. To detect an increase of 1.5 hospital‐free days with > 90% power and a two‐sided significance level of 5%, a total of 920 patients were required.

The combined sample size of 1000 patients provides adequate power for all four primary outcomes within the factorial design. The trial is not powered to detect interactions between interventions; prespecified interaction analyses (Section 3.5) are exploratory and hypothesis‐generating.

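### ICU stay, hospital stay, intubation time and days without delirium treatment are compared by plain Wilcoxon test with no stated role for death, so a mortality difference alone can distort these secondary comparisons

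*SAP article*

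**What the plan says.** Section 3.3.3 (Count Data) lists ICU length of stay together with the outcomes in "hospital length of stay, duration of intubation, days without delirium treatment) will be analyzed using the Wilcoxon" rank-sum test. The effect summary follows: "Results will be presented as medians with interquartile ranges and 95% confidence intervals for the median difference obtained by bootstrapping". The section does not say whether a patient who dies is counted up to death, given a worst value, excluded, or treated as having a competing event.

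No other section fills the gap:

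- Section 2.5.1 gives death a role in days alive outside hospital, and only there.
- Section 3.2.1 uses competing risks to compare causes of death, not to analyse discharge or extubation.
- Section 3.6 deals with missing values, not with durations cut short by death.

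Section 2.6 shows how common death is expected to be. For olanzapine and wakeup, "estimates assumed 35% mortality during initial hospitalization". For dexamethasone and backrest, the calculation is made "assuming an overall mortality of 35% and a 25% relative risk reduction (to 26% mortality), with 85% power".

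**The concern.** About a third of patients are expected to die before discharge, and for two interventions the design looks for a difference in mortality between arms. A rank test on observed durations places a patient who dies on day 2 beside one who goes home on day 2. The arm with more early deaths then tends to look shorter, and the arm with fewer deaths longer, even if the intervention changes nothing about how long survivors stay. Restricting the test to survivors avoids that ranking but compares groups selected by an event after randomization.

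The section leaves open which of these is meant, so the choice could be made after the data are seen. At stake is the reading of the secondary resource and recovery outcomes: a life-saving intervention could be reported as prolonging hospital stay, and a harmful one as shortening it.

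**Working it through.** **1. The plan's own figure.** Inputs from Section 2.6 are 35% versus 26%, 85% power and two-sided 5%. With mean proportion 0.305:

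n = [1.960 × √(2 × 0.305 × 0.695) + 1.036 × √(0.35 × 0.65 + 0.26 × 0.74)]² / 0.09² = 468.4 per group.

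The plan has "significance level of 5%, 468 patients per group are required", so the figure reproduces, and "500 patients per group (1000 total) are planned". The check therefore uses 500 per arm and these mortality rates.

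**2. Survivors' stay.** Section 2.6 takes "a mean of 15 days outside hospital for survivors, yielding a population mean of 9.8 days with an estimated standard deviation of 7 days". Fifteen of 30 days outside hospital leaves about 15 days in hospital, and 0.65 × 15 = 9.75 agrees with the stated 9.8. So survivors' mean stay is set at 15 days in both arms.

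**3. What the Wilcoxon test sees.** Suppose survivors have the same stay distribution in both arms, and so do patients who die. Let θ be the probability that a survivor's stay exceeds that of a patient who dies. Writing each arm as a mixture of the two groups gives

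P(better-survival arm longer) = 0.5 + (0.35 − 0.26) × (θ − 0.5).

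Three things follow. With equal mortality the first bracket is zero, so there is no distortion. If patients who die stay as long as survivors, θ = 0.5 and there is again none. The sign depends on whether θ is above or below 0.5.

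**4. Expected rejection rate.** The null standard error of this probability is √[1001 / (12 × 500 × 500)] = 0.0183. For patients who die at a mean of 3 days, the simulated probability is 0.541, so z = 0.041 / 0.0183 = 2.24. The chance of a significant longer stay is then Φ(2.24 − 1.96) = about 61%.

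**5. Simulation.** There were 2000 trials per row and a two-sided 5% test. Survivors' stay was gamma with shape 3 and mean 15 days; stay of patients who die was gamma with shape 1.5. Time to death is not in the document, so its mean is an assumed range.

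| Mean stay of patients who die (assumed) | P(longer) | Medians, 35% vs 26% arm | Significantly longer in the 26% arm |
|---|---|---|---|
| 3 days | 0.541 | 8.6 vs 10.1 | 62% |
| 5 days | 0.533 | 9.6 vs 10.6 | 44% |
| 7 days | 0.527 | 10.4 vs 11.2 | 33% |
| 10 days | 0.517 | 11.5 vs 12.0 | 14% |
| 15 days | 0.504 | 13.0 vs 13.1 | 4% |

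In the last row, rejections in either direction total 5.4%, close to the nominal level. A second simulation with slightly different assumptions (survivors' SD 8 days, whole-day rounding) gave 56%, 42% and 27% at means of 4, 6 and 8 days. With 35% mortality in both arms it gave rejection rates of 3.6% to 5.2%.

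**6. Intubation.** With survivors' mean assumed at 3 days and the same mortality contrast, patients who die ventilated for a mean of 2 days give 16% of trials significantly longer in the better-survival arm. At a mean of 7 days, 22% are significant and nearly all are shorter. The sign reverses, as the formula in step 3 implies.

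**7. Two ways of handling death.** Ranking deaths worst in the hospital-stay setting gives 70% to 71% of trials significant, all in favour of the better-survival arm, with P = 0.5 − 0.09 × 0.5 = 0.455. Survivors only gives 4% to 6%. That second figure is reassuring only because the simulation made survivors alike in both arms; it does not test selection bias.

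**The case against.** The strongest reply is that these four outcomes are not among the common secondary or tertiary outcomes in Sections 2.5.2 and 2.5.3. Section 2.5.2 sends intervention-specific outcomes to the four protocol papers, which are not shown. Those papers may define the variables so that death is covered; days without delirium treatment might already mean days alive. That possibility stands. But Section 3.3.3 itself fixes the test and the summary for these outcomes without pointing to any such rule. Followed as written, it ranks an early death as a short duration.

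Observed bed-days and ventilator-days are also legitimate descriptions of resource use: fewer days used is true even when death is the reason. That supports reporting them, but not testing them as a treatment effect on duration or recovery.

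A reader might infer more than the document supports, in four ways:

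- That a mortality benefit would reliably produce a significant longer stay. The range runs from 62% down to the nominal level, and the document gives no time to death to place the trial within it.
- That ventilation would also look longer. For intubation the direction can reverse.
- That the Wilcoxon test is itself invalid here. It is usable once deaths are given a rank; the gap is the rule for deaths.
- That the problem is shown for olanzapine and wakeup. Section 2.5.1 expects these to act through recovery and shorter stays rather than directly on mortality, and with equal mortality no distortion arises. The 35% versus 26% contrast belongs to dexamethasone and backrest.

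**Conclusion.** The point stands in limited form. Section 3.3.3 gives death no role in four durations, in a population with 35% assumed in-hospital mortality. Where mortality differs between arms and observed durations are ranked, the comparison mixes the mortality effect with any effect on duration.

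For hospital stay at the plan's 35% versus 26%, the false longer-stay finding ranges from about 62% to 4% of trials. This rests on identical stays in survivors, a survivor mean of 15 days and an assumed mean stay of 3 to 15 days in patients who die. For intubation the direction cannot be predicted from the document. ICU stay and days without delirium treatment share the gap but were not simulated.

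The primary conclusions are not touched. Days alive outside hospital, which counts death, and 90-day mortality are each primary or secondary for all four interventions and will stand beside these results. The change should be made, but it is not critical to the trial's main claims.

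**What to change.** In Section 3.3.3, state how death enters each outcome:

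- Analyse ICU stay, hospital stay and intubation as time to alive discharge or alive extubation with death as a competing event (Aalen–Johansen curves with a cause-specific or subdistribution hazard ratio). Alternatively, keep the Wilcoxon test and give deaths the worst rank.
- Define the delirium outcome as days alive without delirium treatment, so that death scores low.
- Show observed durations and survivors-only medians as description, without a test.
- If a companion protocol already defines any of these, cite it and make the wording agree.

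The cost is a few lines of text and a little more programming, with no new data. The drawback is that the result is no longer a pure duration: a difference may come from survival, from speed of recovery or from both, so it must be reported and read together with mortality.

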#### Ordinal Outcomes

3.3.4

Cerebral Performance Category and modified Rankin Scale at discharge and follow‐up will be analyzed as ordinal outcomes using proportional odds models with robust standard errors clustered by site and other interventions as fixed effects. Results will be reported as odds ratios with 95% confidence intervals. Proportional odds assumptions will be assessed using Brant tests.

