## Background

1

Critical care management after out‐of‐hospital cardiac arrest (OHCA) aims to limit ischemia–reperfusion injury by targeting sedation, hemodynamics, ventilation, and temperature, but optimal strategies to reduce post‐cardiac arrest syndrome‐related morbidity and mortality remain uncertain [1, 2]. Post‐cardiac arrest syndrome comprises a systemic inflammatory response, cerebral and myocardial dysfunction, and the underlying precipitating pathology [3]. It results in high mortality rates and long‐term neurological disability despite contemporary intensive care, including temperature control and organ support. Several potentially modifiable treatment domains in the early post‐resuscitation phase—systemic inflammation, cerebral perfusion and intracranial pressure, duration of sedation, and delirium—are supported by expert consensus based on pathophysiological rationales and observational data but have not been evaluated in large, pragmatic, randomized trials in comatose patients resuscitated from OHCA.

The DANOHCA (Danish Out‐of‐Hospital Cardiac Arrest) trial is an investigator‐initiated, randomized, controlled, multicenter, 2 × 2 × 2 × 2 factorial clinical trial evaluating four distinct interventions in patients who remain comatose after resuscitation from OHCA.

The trial evaluates two pharmacological interventions, that is, high‐dose dexamethasone to control systemic inflammation and prophylactic olanzapine to prevent delirium, and two physiological interventions, that is, elevated backrest positioning to improve cerebral perfusion pressure and early versus late wakeup call to reduce exposure to deep sedation and facilitate earlier hospital discharge. In general intensive care, current guidelines advocate minimal sedation and daily wakeup calls [4]. However, in post‐cardiac arrest care, prolonged deep sedation for 24–48 h has been standard of care since the introduction of targeted temperature management, despite limited evidence [2, 5, 6]. The early wakeup intervention tests whether the principle of minimal sedation also applies after cardiac arrest.

These four interventions target distinct but complementary mechanisms in early post‐resuscitation care, systemic inflammation, delirium, cerebral perfusion, and sedation strategy, aiming collectively to reduce morbidity and mortality after cardiac arrest.

All patients are randomized in a 1:1 factorial design to all four interventions simultaneously.

The four hypotheses are:

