#### Secondary Outcomes

2.5.2

The following secondary outcomes are assessed across all four interventions. Intervention‐specific secondary outcomes are detailed in the four dedicated protocol publications.

Common secondary outcomes for all four interventions include:
All‐cause mortality at 90 days (for interventions where this is not the primary outcome).Days alive outside hospital within 30 days (for interventions where this is not the primary outcome).Cerebral Performance Category and modified Rankin Scale at follow‐up 3–6 months after cardiac arrest.

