### General Principles

3.1

All analyses will be conducted according to the modified intention‐to‐treat principle, including all randomized participants who meet the inclusion criteria and have available outcome data, or imputed outcome data (see missing data section below). Participants who do not fulfill the inclusion criteria will be excluded from analyses. If consent is subsequently withdrawn, data collected prior to withdrawal will be included in the primary analysis in accordance with the EU Clinical Trials Regulations, unless the participant explicitly requests deletion of their data. A per‐protocol analysis will be performed as a sensitivity analysis, including only participants who received all scheduled doses of pharmacologic interventions, adhered to the assigned backrest position for ≥ 80% of the time, and had a wakeup call attempted within the assigned time frames.

Data will be analyzed and reported as four individual trials, with no adjustment for multiple comparisons planned. This approach is justified because almost all previous trials in the hospital phase of out‐of‐hospital cardiac arrest care have been neutral, and all four interventions are accepted without considering potential interactions. If more than one intervention shows a non‐neutral result, interactions between interventions will be evaluated by including pairwise and higher‐order interaction terms in the primary regression models for each intervention, applying the prespecified thresholds defined in Section 3.5 (interaction *p* < 0.01 and absolute effect ≥ 5.6%). If a clinically important interaction is identified, results for the affected interventions will be presented both as overall estimates and stratified by the interacting intervention allocation. All regression analyses will be adjusted for site as a covariate.

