All statistical significance tests will be two‐sided, with a significance level of 5%. No alpha spending or adjustment of the final significance level is required, as the planned interim analysis at 500 enrolled patients is a safety review conducted by the independent data‐monitoring committee without formal efficacy or futility testing (see Section 3.9). Throughout, categorical variables will be presented as counts with proportions, whereas continuous variables will be presented as means ± standard deviations for normally distributed variables or medians (25th–75th percentiles) for nonnormally distributed variables. The normal distribution will be evaluated using quantile‐quantile plots.

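### CPC and mRS are tested with standard errors clustered on only five sites and no few-cluster correction; with the usual normal reference the two-sided error is about 12% or more, not 5%

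*SAP article*

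**What the plan says.** - **Model.** Section 3.3.4 (Ordinal Outcomes) analyses CPC and mRS at discharge and follow-up "using proportional odds models with robust standard errors clustered by site and other interventions as fixed effects", and reports odds ratios with 95% confidence intervals.
- **Clusters.** Section 2.6 (Sample Size): "The trial aims to include 1000 patients across five sites, covering the entire Danish population".
- **Level.** Section 3.1 sets a two-sided 5% level for all significance tests. It plans no multiplicity adjustment across the four interventions.
- **Status.** Section 2.5.2 lists CPC and mRS at 3-6 months as common secondary outcomes of all four interventions.
- **Unit of randomisation.** The Background states: "All patients are randomized in a 1:1 factorial design to all four interventions simultaneously".
- **Site elsewhere.** Section 3.1: "All regression analyses will be adjusted for site as a covariate". Sections 3.2.2, 3.3.1 and 3.3.2 use site as a random effect. Site-clustered standard errors appear only in section 3.3.4.
- **Checks.** Section 3.7.1.3 checks only the proportional odds assumption for these models. The fallback to bootstrapping in section 3.7.1.1 is written for the mixed-effects models.

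**The concern.** A cluster-robust variance estimates uncertainty from the spread of cluster-level score totals. Its justification is that the number of clusters is large; a large number of patients does not substitute. With five sites the estimate rests on five totals that sum to zero, so it carries about four degrees of freedom. The standard error is then very variable and tends to be too small. Dividing by it and comparing with 1.96 rejects too often.

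CPC and mRS are the only functional outcomes in the list of common secondary outcomes. Two scales and four interventions make eight tests at follow-up, with more at discharge. If no intervention had any effect, the expected number of false positives among the eight would be 8 × 0.05 = 0.4 at the nominal level, but 8 × 0.122 = 0.98 at the analytic error rate derived below. A chance finding on neurological outcome, in either direction, becomes clearly more likely, and the plan's own assumption checks would not reveal it.

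**Working it through.** **Inputs from the SAP article.** G = 5 sites and N = 1000 (section 2.6); two-sided 5% (section 3.1); four 1:1 factors allocated to individual patients (Background and section 2.3); site-clustered proportional odds model (section 3.3.4).

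**Assumed, not in the document.** Normal reference for the Wald test; variance factor G/(G−1) = 1.25; site sizes; site effects with SD 0 or 0.3 on the log-odds scale; CPC and mRS distributions (37% in the worst category in the larger simulation).

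**Plan's own figure.** The plan states no operating characteristic for this analysis beyond the nominal 5%. That is therefore the figure to reproduce.

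**Step 1, analytic.** With G clusters the statistic behaves roughly as t with G − 1 = 4 degrees of freedom.

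- With the G/(G−1) factor: P(|t₄| > 1.96) = 12.2%.
- Without it, the effective cut-off is 1.96 × √(4/5) = 1.753, and P(|t₄| > 1.753) = 15.4%.

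**Step 2, simulation.** Maximum-likelihood proportional odds fits, N = 1000, five sites, no treatment effects. Each setting had 1200 data sets × 4 coefficients = 4800 tests, with a Monte Carlo standard error of about √(0.13 × 0.87 / 4800) = 0.5 percentage points. The ranges cover mRS and CPC, both values of the site SD, and models with and without site as a fixed covariate.

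| Site sizes | Clustered, normal, with factor | Clustered, normal, no factor | Clustered, t(4), with factor |
|---|---|---|---|
| 200 each | 11.6-13.6% | 15.0-16.7% | 4.6-5.8% |
| 350/250/180/130/90 | 12.8-14.3% | 16.4-17.9% | 5.1-6.5% |
| 500/250/130/80/40 | 16.0-17.2% | 19.7-21.0% | 7.5-8.4% |

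Model-based standard errors in the same data gave 4.4-5.7% across all settings, which reproduces the nominal 5%.

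A separate simulation (mRS-like outcome, 600 runs per setting, the 16 combinations blocked within site) gave 11-12% with equal sites and 13.5-16% with sites of 400/250/150/120/80. Model-based errors gave 4.5-5.8% there. Blocking within site therefore does not remove the excess.

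**Step 3, coverage.** Coverage is one minus the error rate. An error of 11-16% means nominal 95% intervals cover 100 − 11 = 89% down to 100 − 16 = 84% on average.

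**Step 4, is clustering needed?** Individual patients are randomised to every factor, so each treatment contrast can be made within sites. Differences in prognosis between sites do not bias the contrast or invalidate patient-level standard errors, and model-based errors held their level with site SD 0.3.

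**The case against.** The strongest reply is that the error rate is conditional. Section 3.3.4 names neither a normal reference nor a variance factor, and section 3.11 names only the software. With a t(4) reference most of the excess disappears. This stands, and the rate must be quoted as conditional. It does not rescue the plan: the correction is not prespecified, it still leaves 7.5-8.4% with very unequal sites, and its critical value of 2.776 against 1.96 makes an interval 2.776/1.96 = 1.42 times as wide for the same standard error.

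A second reply is that clustering allows treatment effects to vary between sites. Five clusters cannot support that inference well, and the plan describes its five sites as covering the whole country, so no larger set of sites is being sampled within that population.

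Some stronger readings are tempting but not supported:

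- **A contradiction with section 3.1.** A model can include site as a covariate and also cluster its standard errors, so the two statements are compatible. Nor does the covariate cure the problem: the simulated inflation is about the same with it.
- **Rank deficiency as the cause.** With five site totals summing to zero, the variance matrix has rank at most 4, below the number of parameters in an mRS model (6 cutpoints + 4 allocations = 10). That matters for joint tests of many coefficients. The plan reports single odds ratios, whose error comes from the few clusters and the normal cut-off.
- **Every interval too narrow.** With five clusters the standard error is erratic. Intervals under-cover on average, but a particular one may be too wide.

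**Conclusion.** The point holds for the ordinal outcomes. Clustering on five sites is unnecessary in this design, and with the usual normal reference it does not keep the 5% level: about 12% analytically, about 11-16% in simulation for equal to moderately unequal sites with the G/(G−1) factor, and higher with very unequal sites or without the factor. Average coverage of the nominal 95% intervals is about 84-89% over the 11-16% range. The exact bounds depend on the assumed reference distribution, variance factor, site sizes and outcome distributions. The excess itself appeared in every setting tried with a normal reference.

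A reader might infer that the trial's main conclusions are at risk. They are not: 90-day mortality is analysed by log-binomial regression (section 3.2.1) and days alive outside hospital by the Wilcoxon test (section 3.2.2). The point is therefore one that should be fixed, not one that threatens the primary results.

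**What to change.** Replace the sentence in section 3.3.4 with: a proportional odds model with site and the other three allocations as fixed effects alongside the intervention under study, using model-based (or patient-level robust) standard errors, without clustering on site. This also applies the site-covariate rule of section 3.1 explicitly.

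The cost is one sentence and no new data. Individual intervals may become wider or narrower than under clustering, but their coverage would be close to nominal. If the investigators wish to keep clustering, they should prespecify the few-cluster correction and the reference distribution, and accept the loss of power. Either change should be made before the allocation is unblinded.
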